## Discussion

We have described the protocol of our ongoing pilot clinical study in chronic stroke, where we test safety, feasibility, efficacy and neural markers of upper limb rehabilitation combined with stimulation targeting the PMC in the affected hemisphere. Evidence on the value of paired cortical stimulation in rehabilitation is divided due to theoretical and design-related issues. Stimulating peri-lesional and affected M1 without knowing the individual substrates of recovery creates variability in response
[4,19,67]. Differences in design, such as type of control, blinding and safety-feasibility trade off of varying types of stimulation have further added confusion to evidence of efficacy. Recent trials have also failed at the phase III level due to poor estimation of the magnitude of the placebo effect
[19,68]. Therefore, to prepare for future trials, we propose targeting the PMC in the affected hemisphere with the rationale that it may serve as an alternative locus of recovery. We employ tDCS, which may be safer and feasible to apply online during long-term outpatient rehabilitation; based on its ability to provide a more effective placebo, it permits us to adopt double blinding and sham control, helping estimate the magnitude of placebo. Finally, we identify patient-specific indicators of recovery to stratify responders for design of future investigations.

Knowing markers of response versus non-response to brain stimulation in rehabilitation would not only harmonize evidence in the field, but will also help us select candidates for subsequent trials. Early clinical trials of invasive stimulation showed greater promise of adjuvant stimulation
[8-10] than recent phase III
[15,19], potentially since patients in earlier trials possessed functioning corticospinal pathways
[9] unlike only a few in phase III
[19]. Similarly, rehabilitative outcomes are invariably successful for well-recovered patients
[14,22], unlike for those with moderate/severe paresis
[16,18,31]. Subcortical lesions respond better
[13,29] than massive infarcts of total anterior circulation
[69]. If we find that responsive patients show distinctive characteristics, such as patent and functioning white matter tracts et cetera, then these would serve as entry criteria for the future. Unfortunately it may also mean that stimulation may be more fruitful only for a limited few, but this information would optimize resource allocation. For patients showing limited to no response, we would identify whether functioning of alternate areas (as identified on fMRI) and patency of tracts from other regions (from tractography) may hold greater meaning. A patient-guided approach to utilizing such residual resources will then be created, employing alternate rehabilitation methods and/or stimulating patient-specific loci.

Knowing mechanisms of long-term pairing can help address why chronic effects are not as robust. Even though singular sessions or short-term paradigms show benefit
[11,13,16,22,29,30], trials incorporating long-term training have failed to witness an advantage
[15-19]. Divergent success across short- and long-term studies may also be an effect of dosage. Stimulation may have an initial accelerative effect
[25,32] manifested in the short term, but over the long term, the effect of rehabilitation itself may become robust
[37,70], diminishing the comparative effect size.
[15-19]. Confounding from individual variance may also factor in; if stimulation in rehabilitation were truly effective, its differences from rehabilitation would evolve over time; on the flip side, if all gains were solely related to variance across individuals, then a long-term study would show no difference, and short-term studies would be easily confounded. Short-term designs also have the added advantage of higher treatment fidelity; standardized laboratory-based paradigms can be delivered in short-term approaches more easily
[13,14,22,29,45], whereas longer protocols of clinical rehabilitation suffer from variance in treatment delivery
[8-10,16,17,23-25,30,44]. However, exploring stimulation delivered with long-duration rehabilitation still carries greater clinical utility, despite challenges to adherence and fidelity, because short-term paradigms, though invariably positive, do not correlate with long-term outcomes
[13,14,22,23,29-31,45].

Use of chronic paradigms offers another important advantage, namely, retention. Besides the primary endpoint, we have built a delayed follow up. Initial clinical trials note that groups receiving cortical stimulation retain benefits whereas the ones receiving rehabilitation alone show a dip in performance after the end of training
[8,9]. These delayed benefits, maintained post-stimulation, may be indicative of a neuro-protective effect
[6] that we may be able to infer by completing our 3-month follow up.

Besides duration and retention, we suggest other potential advancements that could help improve the rigor of study design in the field. Creating a sham-controlled, double-blinded approach remains ethically and technically challenging with invasive stimulation
[8-10], and sham conditions created with noninvasive rTMS have not been strongly convincing either
[24,25]. Using tDCS may offer a unique opportunity to create a more valid sham for effective blinding
[62] and provide a better estimation of the placebo effect. Caveats remain to be addressed, however. Is it possible that what is gained in safety-feasibility with tDCS is lost in effectiveness, when relating to more focal methods such as rTMS and invasive cortical stimulation
[4].

Overall, the strengths of our pilot protocol include 1) examining a novel target of stimulation that differs from the classical and contemporary approach; 2) use of a generalizable rehabilitation paradigm that is delivered over the long term to generate true estimates of efficacy, adherence, and retention, thence, utility of brain stimulation; 3) use of a method of stimulation that is low cost, safe, feasible and allows estimation of the magnitude of the placebo effect; and 4) characterization of structural, pathologic, neurophysiologic and functional predictors of response. Despite these strengths, we anticipate challenges. The estimated sample size may be limited. Because others have noted significant effects with similar repeated-measures designs with a total of 14
[30] to 24
[8] patients, we anticipate our pilot exploratory study may generate comparable effects. Nevertheless, we do not wish to undermine the significance of large-scale studies. In fact, our current exploratory study is a step in the direction. The resources of our study and its single-center nature, though, are restrictive in addressing efficacy at that level at this time. Combining imaging and stimulation makes enrollment increasingly difficult and adds greater measurement burden. Also, since the intervention can only be delivered in a hospital setting, poor compliance can affect feasibility. To mitigate such threats, a contracted treatment schedule for CIMT is being followed. If a greater and/or accelerated benefit were to be achieved with tDCS, then the utility of abridged CIMT would be established. Our rationale is derived from our work where tDCS paired with contracted vision rehabilitation promoted gains equivalent to a traditional, longer paradigm
[32,40,71]. Ultimately, our pilot clinical study carries important implications for future trials; utility of an alternate cortical target would inform future transcranial research and investigation of markers of recovery would inform invasive (intracranial) applications of subcortical/deep brain structures that are in translational stages
[72,73].

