### Objectives and hypotheses

In line with our rationale, the objectives of the present pilot clinical study are to: 1) examine the safety, feasibility and effectiveness of CIMT paired with tDCS targeting PMC, versus CIMT delivered alone in alleviating impairments of the paretic hand in patients with chronic stroke; and 2) assess neural markers associated with response to paired paradigm versus CIMT alone.

We hypothesize that the paired approach involving stimulation of PMC in the stroke-affected hemisphere will be more effective than CIMT in improving hand function in chronic stroke. The paired approach will facilitate the individual’s specific neural substrates of recovery and will be safe to employ throughout the length of the study.

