## Methods

### Study design

We use a pilot, randomized, sham-controlled, double-blind clinical study design. Twenty patients are being randomly assigned to PMC tDCS plus CIMT or sham tDCS plus CIMT groups. All outcomes are collected at pretest and at post-test after 5 weeks of intervention. At 3-month follow up, outcomes of hand function are collected to examine retention.

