### Randomization

We are using randomization blocks in sizes of four, where two patients in a block are assigned to PMC tDCS plus CIMT and the other two to the sham tDCS plus CIMT group. Such block randomization prevents the possibility that several patients in a row would get randomized to tDCS or sham tDCS groups in the early part of the study. The order of patients in blocks is random, generated using an online tool. Allocations are concealed in an opaque envelope and hidden in a locked cabinet with restricted access; they are opened by an investigator not involved in data collection or analysis before the first day of treatment.

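### With both arms on the same contracted CIMT and no CIMT arm without sham, the trial can neither establish abridged CIMT nor measure the placebo effect, as the Discussion says it can

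*Protocol article*

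**What the plan says.** **Arms.** Study design: "Twenty patients are being randomly assigned to PMC tDCS plus CIMT or sham tDCS plus CIMT groups". Randomization confirms equal allocation in blocks of four: "two patients in a block are assigned to PMC tDCS plus CIMT and the other two to the sham tDCS plus CIMT group". The CIMT section puts all patients on two 30-minute sessions a day, 3 days a week, for 5 weeks. It sets this against the usual modified programme of one 30-minute session, three times a week, for 10 weeks. Mitt wear is also reduced, from 5 to 2 hours per weekday. The article describes no arm with standard-length CIMT, with CIMT but no sham, or without treatment.

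**Abridged CIMT.** The Discussion paragraph on anticipated challenges concludes: "If a greater and/or accelerated benefit were to be achieved with tDCS, then the utility of abridged CIMT would be established". The next sentence supports this with earlier work in vision rehabilitation, where a shortened programme with tDCS matched a longer traditional one.

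**Placebo.** The opening paragraph of the Discussion says of tDCS that "it permits us to adopt double blinding and sham control, helping estimate the magnitude of placebo". The later list of strengths includes a stimulation method that "allows estimation of the magnitude of the placebo effect".

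**Comparator label.** Objective 1 compares the paired treatment "versus CIMT delivered alone in alleviating impairments of the paretic hand in patients with chronic stroke". Objective 2 and the hypothesis use similar short forms.

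**The concern.** Both Discussion claims are affirmative statements about what the data will show, and each needs a comparison group that the trial does not have.

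A difference between active and sham tDCS is a statement about tDCS. Because both arms receive the same contracted CIMT, the schedule cancels from that difference. A reader who takes the conclusion at face value could regard 15 visits as shown to be an adequate replacement for 30, with no patient on the longer schedule to support it.

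A sham arm controls for placebo response but does not measure it. The between-arm difference removes the placebo component, and the within-arm change adds it to five weeks of a therapy that the article itself expects to work. The distinction matters because the Discussion attributes some late-phase failures to misjudging the placebo response, so readers may look to this pilot for that quantity.

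**Working it through.** The protocol gives no figure to reproduce on this point. The question is which effects two arms can identify, and that can be checked directly.

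**Inputs**
- Two arms, 1:1 (Study design; Randomization).
- Same contracted CIMT for all patients; the longer programme is described but is not an arm (CIMT section).
- Sham: 1 mA for 30 to 60 seconds, then turned off (tDCS section).

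**Step 1: write each arm's mean pre-to-post change as a sum.** Let T = time and retest, C = contracted CIMT, P = placebo response to apparent stimulation, S = specific effect of active tDCS, L = standard-length CIMT. Assume that the parts add.

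| Arm | T | C | P | S | L |
|---|---|---|---|---|---|
| tDCS + CIMT | 1 | 1 | 1 | 1 | 0 |
| sham + CIMT | 1 | 1 | 1 | 0 | 0 |

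This matrix has rank 2. An effect is estimable only if its coefficients are a linear combination of the two rows.

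**Step 2: check each target.**

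| Target | Coefficients | Estimable? |
|---|---|---|
| Active over sham tDCS, given contracted CIMT | S | Yes (row 1 − row 2) |
| Total change under sham + CIMT | T + C + P | Yes (row 2) |
| Placebo effect | P | No |
| Abridged minus standard CIMT | C − L | No |
| tDCS + CIMT versus CIMT without sham | P + S | No |

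The column for L is zero in both arms, so no analysis of these data can yield C − L. T, C and P have identical columns, so only their sum is determined. Purely as an illustration (the protocol gives no such figure), if the sham arm gained 4 UEFM points, then T + C = 4 with P = 0 and T + C = 0 with P = 4 would fit equally well.

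**Step 3: what extra arms would identify.**
- An arm of contracted CIMT without sham has mean T + C. Then (T + C + P) − (T + C) = P, so the placebo effect becomes estimable.
- An arm of sham plus standard-length CIMT has mean T + L + P. Then (T + C + P) − (T + L + P) = C − L, so the schedule comparison becomes estimable.

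Neither arm is in the trial.

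**Step 4: how far the schedules differ.**
- Supervised time: 2 × 30 × 3 × 5 = 900 minutes contracted; 1 × 30 × 3 × 10 = 900 minutes usual.
- Visits: 3 × 5 = 15 versus 3 × 10 = 30.
- Mitt hours: 2 × 5 × 5 = 50. The usual total depends on how long the 5 hours per weekday runs, which the article does not state: 5 × 5 × 10 = 250 over 10 weeks, or 5 × 5 × 5 = 125 over 5 weeks.

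The schedule is therefore shortened in calendar time, visits and mitt hours, but not in supervised minutes, and equally in both arms. How it compares with the longer schedule is a real clinical question that this trial does not test.

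**The case against.** **The placebo wording is loose, not wrong.** In the list of strengths the subject is tDCS as a method, contrasted with invasive stimulation and rTMS, whose shams the article considers difficult or unconvincing. "Placebo effect" can also mean the response seen under the placebo condition. That quantity is estimable and is useful for planning a sham-controlled follow-on trial. This stands in part: the useful quantity exists. The text still names the magnitude of placebo, which readers will take as the component and not as the total that includes CIMT.

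**The abridged-CIMT sentence is conditional.** It could mean that the contracted schedule is useful when paired with tDCS, and no hypothesis or analysis depends on it. The second half is true. But the sentence says that the usefulness would be established, and the one that follows supports it by equivalence to a longer programme. The implied comparison is with a schedule that nobody in the trial receives.

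**Two stronger readings are tempting, and the article supports neither.**
- A reader might infer that the objectives contradict the design, because they contrast the paired treatment "versus CIMT delivered alone in alleviating impairments of the paretic hand" while patients are randomised to "PMC tDCS plus CIMT or sham tDCS plus CIMT groups". The abstract, Study design, Randomization, tDCS and Sample size estimation sections all make the control sham tDCS plus CIMT, so the objectives use shorthand.
- A reader might infer that the investigators will treat the sham-arm gain as placebo and mis-size the next trial. The remark about preparing for future trials governs the choice of the premotor target. Statistical and data analyses contains no placebo analysis. Sample size estimation says the pilot will hand on the effect size for premotor tDCS and neural markers.

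**Conclusion.** Two Discussion claims are wrong as written. The more serious is that a tDCS benefit would establish abridged CIMT: zero patients receive the comparison schedule, so the randomised contrast carries no information on it. The second is that the magnitude of the placebo effect can be estimated: only the sum of CIMT, retest, time and placebo in the sham arm can be.

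The result does not depend on sample size, variance or choice of model. Additivity was assumed for clarity; allowing interactions adds unknowns and does not make either target estimable from two arms. An analysis plan that is not shown could not repair this, because the missing element is a comparison group.

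The scope is limited. Active versus sham tDCS, given the contracted CIMT, remains a valid randomised comparison, and the sample size, significance level and primary analysis are unaffected. The comparator label in the objectives is a wording inconsistency only.

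**What to change.** 1. **Discussion, paragraph on challenges:** delete the conclusion about abridged CIMT, or limit it to the effect of active over sham tDCS when both are given with the contracted schedule.
2. **Discussion, opening paragraph and the paragraphs on sham rigour and strengths:** replace the claims to estimate placebo with: change under sham tDCS plus CIMT (all components combined), with 95% CI.
3. **Objectives and hypotheses (minor tidying):** name the comparator as sham tDCS plus CIMT in both objectives and in the hypothesis.

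The cost is wording and narrower claims. No patients, visits or tests are added. Making the two wider claims estimable would need additional arms, which this correction does not require.

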### Trial status

The trial is actively enrolling.

## Abbreviations

CIMT: Constraint-induced movement therapy; Fc: Functional connectivity; fMRI: Functional magnetic resonance imaging; GCP: Good clinical practice; M1: Primary motor cortex; NIH: National Institutes of Health; PMC: Premotor cortex; rTMS: Repetitive transcranial magnetic stimulation; tDCS: Transcranial direct current stimulation; TMS: Transcranial magnetic stimulation; UEFM: Upper extremity Fugl-Meyer.
